#### Usual care

Patients in group two will receive ‘usual care’ only. Placebo will include the aforementioned preoperative administration of 2 hard jelly capsules (dimension = 0), containing an orange-swedish microcrystalline cellulose.

### Outcomes

The primary outcome measure in this trial is postoperative graft survival after LT. The secondary outcomes of interest are patient survival, hospitalization stays, and all transplant-related complications in terms of the multi-tier Clavien grading system after LT. The grading system is used in order to identify a significant relation into two homogenous groups of liver transplanted patients, which only differ for Simvastatin or non-administration regimen utilizing the same procedure, with identical surgical instruments, and medical and nursing skilled staff. Baseline data on graft function and patient performance status will be collected immediately prior to discharge from the recovery unit (T0). Follow-up measures will be collected at three time points**:** 3-month (T1), 6-month (T2) and 12-month (T3)**,** after LT (see Fig. 1). All participants will be routinely evaluated with a post-reperfusion liver biopsy (sample), intensive care monitoring, daily laboratory and ultrasound examinations for the first week after the operation and when required during their hospital stay.

### Sample size

We hypothesize that Simvastatin’s protective effects may occur in the liver during the harvesting procedure from the deceased donor and could significantly ameliorate post-LT outcomes. To reach the above-mentioned goals, we decided to recruit 106 patients. This sample size achieves 90% power to detect a difference of 14.6% between the two groups survival using a one-sided binomial test. The target significance level is 0.05. These results assume a null hypothesis that the proportion of the group with the standard procedure is 0.85.

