## Background

Liver transplantation (LT) is the treatment of choice for end-stage liver disease. Ischemia/reperfusion (I/R) injury during the conventional cold storage and preservation of donated livers is a key determinant of graft function after LT. Hypoxia and reperfusion activate innate mechanisms of inflammation that cause injury and underline delayed graft function. [1–3] I/R injury causes almost 10% of early organ failure and can lead to the higher incidence of both acute and chronic rejection. [4, 5] Simvastatin suppresses the inflammatory effect in vascular endothelial cells, thereby protecting the liver against I/R injury and its effects on grafts from extended-criteria donors. [6–9] Statins or HMG-CoA inhibitors were primarily designed to decrease cholesterol levels. However, they have also shown to have beneficial cholesterol-independent effects, such as up-regulating the expression of the vasoprotective transcription factor Kruppel-like factor 2 (KLF2) and consequently, its derived transcriptional programs. Simvastatin protected healthy and steatotic rat livers undergoing cold storage and warm reperfusion before transplantation. [10, 11]

While the issue of I/R injury after LT has been addressed several times and pathophysiology of this entity has been extensively investigated in the context of pre-clinical studies, the attempts to solve this clinical problem have been scarce and unstandardized. This proposal offers a more targeted method of stratifying the differences on the liver sinusoidal milieu. The differences will be obtained with neither a complex therapeutic approach of combining different pharmacologic strategies nor the usage of machine perfusion methods, but by the sole cost of a single drug/placebo administration. In this novel approach, the infusion of Simvastatin will be applied directly into the donor liver’s portal vein after donor hepatectomy. The clinical trial allows avoidance of systemic infusion, so the protocol could also be applied in cases of multiorgan deceased donor retrievals.

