### Donor shortage

LT is the only life-saving therapy for most types of end-stage liver disease. In Italy, the overall rate of cadaver donation is 22.2 donors per million per year, and in some regions, like Sicily, the rate is 12.6 donors per million per year. In the past few years, IRCCS-ISMETT, a transplant hospital in Sicily, has been committed to counteracting this organ shortage. Over the years, the number of transplants has steadily increased thanks to marginal donors, living donors, and split LT. ISMETT has implemented techniques and strategies to most efficiently use valuable resources in order to maintain a high level of LT. From July 1999 till May 2014, we performed 902 LTs for adults: 755 (84%) were performed by using 601 whole livers (80%), 99 (13%) were living-related LTs, and 55 (7%) were split LTs. The one-year survival rate (cadaveric liver transplantation) is 85.4%. [12–14]

The shortage of organs led to the use of steatotic liver grafts from extended-criteria deceased brain donors (DBDs), even though these livers are more susceptible to I/R injury and have poorer outcomes than non-steatotic livers. Preclinical studies have demonstrated that the negative effects of I/R can be prevented by adding Simvastatin to the cold preservation solution shortly before procurement to protect both parenchymal and endothelial components of the liver after warm reperfusion.

The proposed project aims to be the first prospective randomized clinical trial to prove the efficacy of Simvastatin in preventing I/R injury and expand the donor pool.

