#### Statistical analysis

Intention-to-treat analysis will be applied. Quantitative variables will be compared with the Student t-test or the Wilcoxon rank-sum test and categorical variables will be compared with the chi-squared test or Fisher’s exact test as appropriate. No a-priori criteria will be set for an early end of the study. Data will be analyzed according to the 2 × 2 randomized factorial study design. All of the phases will follow the Consolidated Standards of Reporting Trials 2010 Statement to improve the reporting of parallel-group randomized controlled trial, enabling readers to understand the trial’s design, conduct, analysis. and interpretation as well as to assess the validity of its results. It will be achieved through complete transparency from study investigators. All analyses and graphics were performed in the R statistical computing environment, version 3.4.3.

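### The 90% power rests on an unprinted 99.6% graft survival, and the planned analysis tests, as usually applied, deliver about 87% one-sided or 77% two-sided

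*Protocol article*

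**What the plan says.** The Sample size section of the protocol article says "we decided to recruit 106 patients" and continues: "This sample size achieves 90% power to detect a difference of 14.6% between the two groups survival using a one-sided binomial test". It adds "The target significance level is 0.05" and takes 0.85 as the proportion surviving under the standard procedure. The Abstract repeats the 106, the 90%, the 14.6% and the one-sided test, but not the 0.85. Neither place gives the survival rate assumed under simvastatin.

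The Statistical analysis section does not mention a one-sided binomial test. It says that "categorical variables will be compared with the chi-squared test or Fisher’s exact test as appropriate", and gives no sidedness.

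For the centre's own experience, the Donor shortage section reports, in per cent: "The one-year survival rate (cadaveric liver transplantation) is 85.4".

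**The concern.** A reader who sees 90% power for 106 patients will assume that the trial can detect a realistic benefit. The only rate that fits the stated inputs is 99.6% survival on simvastatin, which is near-total elimination of graft loss. The 14.6 points also equal 100 minus the reported 85.4%, the whole historical shortfall from perfect survival, although the article does not say that the figure was obtained this way.

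The power is also quoted for one test while the analysis section names others. With so few losses the choice of test matters. If power is overstated, a non-significant result may be read as evidence that simvastatin does not work when the trial had little chance of showing a smaller benefit.

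**Working it through.** **Inputs.** From the Sample size section: 106 patients, control survival 0.85, difference 0.146, one-sided 0.05, power 90%. Assumed: 1:1 allocation (53 per arm), no dropout, and no allowance for the interim looks.

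**1. Reproduce the plan's figure.** Simvastatin survival = 0.85 + 0.146 = 0.996. Unpooled normal approximation:

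n per arm = (z₀.₉₅ + z₀.₉₀)² × [p₁(1−p₁) + p₂(1−p₂)] / d²
= (1.645 + 1.282)² × [0.85×0.15 + 0.996×0.004] / 0.146²
= 8.564 × 0.131484 / 0.021316 (8.564 uses unrounded z-values)
= 52.8, so 53 per arm and 106 in total.

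Power at 53 per arm is 90.1%. The plan's figure reproduces. The pooled formula gives 88.9% power and 56 per arm. A fall of 14.6 points, to 0.704, gives only 56 to 58%, so the upward reading is the one that fits.

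**2. What 99.6% means in events.** Controls: 53 × 0.15 = 7.95 losses. Simvastatin: 53 × 0.004 = 0.21. Total 8.16, or 4.08 per arm under the null.

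**3. Power of the tests named for the analysis, at 85% vs 99.6%.** Exact enumeration of two binomials with n = 53. The rule in the last row is an assumed, common reading of "as appropriate": Fisher if an expected count is below 5, otherwise uncorrected chi-squared.

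| Test | One-sided 0.05 | Two-sided 0.05 |
|---|---|---|
| Uncorrected chi-squared (pooled z) | 97.1% | 91.3% |
| Fisher's exact | 87.1% | 76.8% |
| Rule: Fisher if expected count < 5 | 87.1% | 77.3% |

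Fisher is triggered in about 70% of trials at these rates. One-sided Fisher alone first reaches 90% at 57 per arm (114 in total).

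One table shows why the test matters. With 4 losses against 0, the pooled z is (4/53) / √[(4/106)(102/106)(2/53)] = 2.04, significant even two-sided. One-sided Fisher gives C(53,4)/C(106,4) = 292,825/4,967,690 = 0.059, which is not significant.

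**4. Power for smaller benefits, 53 per arm, one-sided 0.05.**

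- 85% vs 95%, planning formula: 0.10 / √[(0.1275 + 0.0475)/53] − 1.645 = 1.740 − 1.645 = 0.095, power 54%. Exact one-sided chi-squared: 55%. Rule from step 3: 47% one-sided, 37% two-sided.
- 85% vs 90%, planning formula: 0.05 / √[(0.1275 + 0.09)/53] − 1.645 = 0.781 − 1.645 = −0.864, power 19%. Exact one-sided chi-squared: 19%.

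At 95% the expected losses are 7.95 + 2.65 = 10.6, or 5.3 per arm. Chi-squared would then more often apply, so Fisher-only power is not the right headline for that case.

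**The case against.** The strongest reply is that the Sample size statement is true as far as it goes. It claims 90% power for that difference and that test, and the sum confirms it. A reader might infer that the calculation is wrong; the documents do not support that.

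Second, Fisher is not the only test named. Uncorrected chi-squared, equally available under a sentence that covers all categorical variables, exceeds 90% with either sidedness. A reader might infer that Fisher is the planned test; the text does not say so. The shortfall depends on how "as appropriate" is read. The small-count rule is its ordinary reading, but it remains an assumption.

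Third, the need for exactly 99.6% belongs to the normal approximation. Exact one-sided chi-squared has 93.3% power at 99.0% survival and 89.3% at 98.5%. That stands, but those rates also mean near-total elimination of loss.

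Fourth, a reader might use the Background statement that "I/R injury causes almost 10% of early organ failure" to fix a ceiling on the achievable benefit. It cannot bear that weight: it may mean 10% of grafts or 10% of failures, it concerns early failure while follow-up runs to 12 months, and the same sentence adds rejection as a further consequence of the injury. A reader might also suspect that the 85.4% includes split grafts, which the trial excludes. The article does not say so, and no figure here depends on it.

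Finally, the choice of primary test may be settled in an analysis plan that is not shown. That would excuse silence. It does not excuse printing a power for one test and then naming others, without sidedness.

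**Conclusion.** The point holds as a stated power that the stated analysis rule, on its ordinary reading, does not deliver, resting on a target that the article does not disclose. It is not an arithmetic error. At the planned rates the rule gives about 87% one-sided or 77% two-sided against the stated 90%; uncorrected chi-squared alone would give 97% or 91%. The more consequential weakness is the effect size: the planning formula gives about 54% at 95% survival and 19% at 90%. Severity is moderate, because the correction changes no patient numbers or conduct but does change how the primary result should be read. The figures rest on the assumptions listed with the inputs, and the 87% and 77% also on choosing Fisher when an expected count is below 5.

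**What to change.** Keep 106 patients and make four changes of wording.

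1. In the Abstract and the Sample size section, print the assumed rates, 85.0% versus 99.6% graft survival, with 53 per arm (if allocation is 1:1) and the formula used (unpooled normal approximation, one-sided 0.05).
2. Name one primary test and its sidedness, the same in the Sample size and Statistical analysis sections.
3. Quote the power of that test at those rates: 87% one-sided or 77% two-sided for Fisher; 97% or 91% for uncorrected chi-squared.
4. Add the power at smaller effects: about 54% for 85% versus 95% and about 19% for 85% versus 90%, by the planning formula or one-sided chi-squared. If Fisher is chosen, recompute these for Fisher.

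The cost is rewording and, depending on the test chosen, a less favourable power statement. No extra patients are needed.

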**Patient and methods:**

We propose a prospective, double-blinded, randomized phase 2 study of 2 parallel groups of eligible adult patients. We will compare 3-month, 6-month, and 12-month graft survival after LT, in order to identify a significant relation between the two homogenous groups of LT patients. The two groups only differ by the Simvastatin or placebo administration regimen while following the same procedure, with identical surgical instruments, and medical and nursing skilled staff. To reach these goals, we determined that we needed to recruit 106 patients. This sample size achieves 90% power to detect a difference of 14.6% between the two groups survival using a one-sided binomial test.

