### Interim analysis

Two interim analyses of drug tolerance and efficacy will be performed 6 months after the trial enrollment starting, and when 75% of participants have been enrolled in the trial, respectively. The level of significance will maintain an overall *P* value of 0.05 and be calculated according to the O’Brien-Fleming stopping boundaries. [16]

The DSMB will be instituted as an independent group of experts that will advise the clinicians and the study investigators, without direct involvement in the conduct of the study, nor financial, proprietary, professional, or other interests that may affect impartial, independent decision-making. The ISMETT Director of the Department for the Treatment and Study of Abdominal Diseases and Abdominal, the ISMETT Medical and Scientific Director and the primary investigator (PI) will have primary responsibility for the DSMB formation and for identifying the DSMB Chair and the terms of membership for the entire duration of the study. The DSMB will deliberate processes, including event triggers that would call for an unscheduled review, stopping guidelines, unmasking (unblinding) and voting procedures prior to initiating any data review. ISMETT investigators will collect, assess, report, and manage solicited and spontaneously reported adverse events and other unintended effects of trial interventions or trial conduct.

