## Discussion

This trial is the first to rigorously evaluate the effect of preoperative DBD treatment with the administration of Simvastatin on LT outcomes. The use of Simvastatin could reduce donor liver damage and decrease the length of hospital stay and the rate of complications. There is a remote probability of liver damage with the use of statins. However, Simvastatin is a well-known drug with a minimal reported risk of liver damage compared with the other statins. The factorial design of the trial enables a head-to-head comparison of the individual and cumulative effects of this intervention, which should provide valuable evidence to inform clinical practice.

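### The 106 patients are sized on a one-sided 0.05 test, but the tests named for analysis have no direction, the interim boundary has no side, and Fisher's test does not deliver the stated 90% power

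*Protocol article*

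**What the plan says.** - **Sizing.** The Sample size section sets 106 patients, 90% power, a control proportion of 0.85 and a 14.6-point difference "between the two groups survival using a one-sided binomial test. The target significance level is 0.05". The abstract repeats the claim: "This sample size achieves 90% power to detect a difference of 14.6% between the two groups survival using a one-sided binomial test".
- **Final analysis.** The Statistical analysis section is generic: "categorical variables will be compared with the chi-squared test", or with Fisher's exact test as appropriate. It gives no side and no alpha, and does not name the test for graft survival. No other method listed there suits graft survival at a fixed time point.
- **Interim analysis.** Two looks are planned. "The level of significance will maintain an overall" P value of 0.05 under O'Brien-Fleming boundaries. No side is given.

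The only side stated anywhere in the article is one-sided.

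**The concern.** The sizing fixes a test, a side and an alpha. The analysis section then names other tests and carries over neither the side nor the alpha. Pearson's chi-squared statistic squares the difference, so in its ordinary form it has no direction. Fisher's test has to be told its direction, and the article does not tell it.

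Three things depend on this:

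- whether a borderline graft-survival result counts as positive;
- whether the trial has the power it claims under the test that will be run;
- which O'Brien-Fleming boundary the monitoring board applies, since the boundary cannot be computed without a side.

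**Working it through.** **Inputs.** Control graft survival 0.85, difference 0.146 (so 0.996 on simvastatin if the difference is a benefit), alpha 0.05 one-sided, power 0.90 and total 106, all from the Sample size section. The allocation ratio is not stated; 1:1 is assumed, giving 53 per arm.

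**Step 1: reproduce 106.** Normal approximation, unpooled variance:

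n per arm = (z_alpha + z_power)² × [p1(1 − p1) + p2(1 − p2)] / (p2 − p1)²

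- Variance sum: 0.85 × 0.15 + 0.996 × 0.004 = 0.1275 + 0.003984 = 0.131484. Squared difference: 0.146² = 0.021316.
- One-sided 0.05: (1.645 + 1.282)² = 8.564, so n = 8.564 × 0.131484 / 0.021316 = 52.8, i.e. 53 per arm and 106 in total.
- Two-sided 0.05: (1.960 + 1.282)² = 10.507, so n = 64.8, i.e. 65 per arm and 130 in total.

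Power at 53 per arm by this formula: 0.146 / √(0.131484/53) = 2.931. Then Φ(2.931 − 1.645) = 0.901 one-sided and Φ(2.931 − 1.960) = 0.834 two-sided. The pooled-variance version gives 112 one-sided (power 0.889 at 53 per arm) and 136 two-sided. Only the one-sided versions come close to 106, so the word one-sided in the sizing is not a slip.

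**Step 2: exact power of the named tests.** All 53 v 53 tables were enumerated at 0.85 v 0.996, rejecting at p ≤ 0.05, with no interim looks:

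| Test | One-sided | Two-sided |
|---|---|---|
| Fisher's exact | 0.871 | 0.768 |
| Chi-squared, continuity-corrected | 0.871 | 0.768 |
| Chi-squared, uncorrected | 0.971 | 0.913 |

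Fisher's test misses 90% on either side; uncorrected chi-squared meets it on either side. Which one applies is left to appropriateness. Under the usual rule of thumb (Fisher when the smallest expected count is below 5; an assumption, as the article gives no rule), Fisher is chosen whenever total losses are below 10. Expected losses at the design alternative are 53 × (0.15 + 0.004) = 8.2, and the probability of fewer than 10 is about 0.71.

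**Step 3: borderline results, losses on control v simvastatin.**

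- 8 v 2: Fisher p = 0.046 one-sided, 0.093 two-sided. Uncorrected chi-squared gives 0.023 and 0.046, so this table is split by Fisher only.
- 7 v 1: Fisher p = 0.030 one-sided, 0.060 two-sided.
- 9 v 3: uncorrected chi-squared p = 0.033 one-sided, 0.066 two-sided. With continuity correction it is 0.063 and 0.125, negative on both, so this split needs the uncorrected test.

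Probability of a table that is positive one-sided and negative two-sided, control loss 15%:

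| Simvastatin loss | Fisher | Uncorrected chi-squared |
|---|---|---|
| 0.4% | 0.103 | 0.059 |
| 3% | 0.162 | 0.143 |
| 5% | 0.148 | 0.139 |
| 7% | 0.113 | 0.117 |
| 15% (no effect) | 0.016 | 0.025 |

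**Step 4: interim boundary.** O'Brien-Fleming-type boundaries were computed with the second look at 75% of information (taken as equal to enrolment) and the first assumed between 20% and 50%. The final critical value is z of about 1.72 if the overall 0.05 is one-sided and about 2.01 if two-sided (nominal one-sided p about 0.043 and 0.022). At the 75% look it is about 2.0 against about 2.3 to 2.4.

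**The case against.** The strongest reply is that the article never says two-sided. The overall 0.05 of the interim section matches the 0.05 of the sizing, Fisher's test can be run one-sided, and a 2 × 2 chi-squared has a signed z form. One-sided 0.05 throughout is therefore a possible reading, and the side of the final test is often left to an analysis plan. This stands as far as it goes. It rules out calling the passages contradictory, or calling 106 an arithmetic error. It does not remove the mismatch: even read as one-sided throughout, Fisher's test has 0.87 power, not 0.90.

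Four stronger readings are tempting but not supported:

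- **That one result would be both positive and negative.** This needs a stated two-sided rule, and there is none. The result is positive or negative depending on the reading.
- **That following the analysis section always costs power.** Two-sided uncorrected chi-squared keeps 0.913.
- **That the two-sided power is 83%.** That is the normal formula of step 1. It is the power of neither named test, and it leaves out the interim looks.
- **That one-sided 0.05 is wrong here because harm goes untested.** The Discussion does concede that "There is a remote probability of liver damage with the use of statins", and one-sided 0.05 accepts a two-sided p of up to 0.10. But the side is openly declared in a phase 2 trial with a directional hypothesis, and the Monitoring section has the board review adverse events and allows early termination for safety. The choice of side is a trade-off for the sponsor.

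**Conclusion.** The point holds as a mismatch between the sizing test and the tests named for analysis. The 106 patients are reproduced only at one-sided 0.05 with a normal approximation, while the analysis tests carry no direction and the interim boundary no side. If Fisher's test is used, the claimed 90% becomes about 0.87 one-sided or 0.77 two-sided, before any interim cost; uncorrected chi-squared does not have this shortfall. For true simvastatin losses of 0.4% to 7% against 15%, roughly 6% to 16% of trials would end where the conclusion turns on the unstated side.

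These figures assume 53 per arm, graft survival compared as a proportion at one time point, and 0.996 as the simvastatin proportion for power. The boundary values also rest on the assumed timing of the first look.

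**What to change.** Name one primary test for graft survival, with one side and one alpha, and use them in the abstract and in the Sample size, Interim analysis and Statistical analysis sections.

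- **If the declared one-sided 0.05 is kept:** name the directional test (one-sided Fisher or signed z, alternative that simvastatin is better), state that the O'Brien-Fleming boundaries are one-sided, and report a matching 90% confidence interval.
- **If two-sided 0.05 is chosen:** state two-sided boundaries and report a 95% confidence interval.

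In either case keep 106 patients and restate the power as computed for the named test and boundaries, rather than carrying over 90% or substituting 83%.

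The cost is wording in four places and one power calculation, with no added patients or procedures. The stated power may be less favourable. The choice should be fixed before the first interim look; recruitment has been open since 30 June 2018, so a look at six months falls at the end of December 2018. If it has already taken place, people without access to comparative results should make the choice.
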